## Abstract

**Background:**

There is limited information from low and middle-income countries on learning outcomes, provider satisfaction and cost-effectiveness on the *day of birth care* among maternal and newborn health workers trained using onsite simulation-based low-dose high frequency (LDHF) plus mentoring approach compared to the commonly employed offsite traditional group-based training (TRAD). The LDHF approach uses in-service learning updates to deliver information based on local needs during short, structured, onsite, interactive learning activities that involve the entire team and are spaced over time to optimize learning. The aim of this study will be to compare the effectiveness and cost of LDHF versus TRAD approaches in improving knowledge and skill in maternal and newborn care and to determine trainees’ satisfaction with the approaches in Ebonyi and Kogi states, Nigeria.

**Methods:**

This will be a prospective cluster randomized control trial. Sixty health facilities will be randomly assigned for *day of birth care* health providers training through either LDHF plus mobile mentoring (intervention arm) or TRAD (control arm). There will be 150 trainees in each arm. Multiple choices questionnaires (MCQs), objective structured clinical examinations (OSCEs), cost and satisfaction surveys will be administered before and after the trainings. Quantitative data collection will be done at months 0 (baseline), 3 and 12. Qualitative data will also be collected at 12-month from the LDHF arm only. Descriptive and inferential statistics will be used as appropriate. Composite scores will be computed for selected variables to determine areas where service providers have good skills as against areas where their skills are poor and to compare skills and knowledge outcomes between the two groups at 0.05 level of statistical significance.

**Discussion:**

There is some evidence that LDHF, simulation and practice-based training approach plus mobile mentoring results in improved skills and health outcomes and is cost-effective. By comparing intervention and control arms the authors hope to replicate similar results, evaluate the approach in Nigeria and provide evidence to Ministry of Health on how and which training approach, frequency and setting will result in the greatest return on investment.

**Trial registration:**

The trial was retrospectively registered on 24th August, 2017 at ClinicalTrials.Gov: NCT03269240.

**Electronic supplementary material:**

The online version of this article (10.1186/s12913-018-3405-2) contains supplementary material, which is available to authorized users.

## Background

The competency of frontline birth attendants, particularly on the *day of birth care*, cannot be over-emphasized, as absence of knowledgeable and skilled service providers may cost lives or result in lifelong morbidity and its consequent socio-economic impacts. Research evidence has shown poor availability of skilled birth attendants in Nigeria and the need for evidence-based in-service training of all skilled birth attendants in order to improve competencies and maternal/newborn outcomes [1, 2].

Currently, in-service training of healthcare providers in Nigeria has assumed a traditional lecture-based, off-site or classroom approach of just a few service providers per site at a time. This approach to training can be costly, both in terms of individual provider costs as well as with regard to the opportunity costs of removing providers from clinical practice for extended period of time. Additional limitations in numbers of providers that can be trained in a single deployment can mean that only a small proportion of those engaged in delivery of a particular service receive added capacity building and ultimately, impacts on quality of facility services remain unchanged. When those providers return to their work stations, they often face challenges implementing new or updated skills because the entire team has not been reached which may constitute a barriers. Besides, providers’ turnover due to transfers, resignations, retirements and movement to other sectors also constitute barrier when they involve those who have been trained.

While it is important to increase coverage of maternal and newborn care, there is a need to improve the quality of services provided at health facilities. Evidence from a systematic review has shown that techniques such as simulation, practice and feedback are more effective than lecture and reading, and repetitive rather than single interventions result in better learning outcomes [3]. It is also known that settings similar to the work environment improved skill acquisition and performance of healthcare workers. These findings have driven Jhpiego’s shift into simulation and practice-based, shorter but repeated, workplace-based training. However, one of the limitations of this review was the severe lack of quality data from low- and middle-income countries (LMICs). Testing these approaches in LMICs is important to validate if these findings on technique, frequency, setting and media used to deliver instruction are replicable and feasible.

The LDHF approach uses in-service learning updates to deliver information based on local needs during short, structured, onsite, interactive learning activities that involve the entire team and are spaced over time to optimize learning. It also involves brief, ongoing activities (e.g., skills practice, team drills, games, and quality improvement activities) at the job site to sustain learning and support clinical decision-making.

The principles of the LDHF approach include:Competency-focused learning activities concentrates on what providers “need to know”—eliminating what is “nice to know.”Simulation- and case-based learning focuses on skills practice, problem-solving, role-play, and other interactive exercises. Dosing and frequency depend on topic, extent of the learning gap, and learner characteristics.Appropriately spaced, brief periods of learning deliver targeted information in 1 day or over several days.Team-focused training ensures that all providers have updated clinical practice and can work together to implement improvements in care.Facility-based training decreases absenteeism, improves teamwork, addresses onsite barriers, and promotes changes to provider performance.Ongoing practice and quality improvement activities reinforce learning and transfer to clinical practice.Facility-based peer staff coach others as they practice or engage in interactive exercises after learning to increase compliance and improve performance and outcomes.

Gaps exist in high-quality evidence from Nigeria and other developing countries on the effectiveness of simulation-based LDHF/m-Mentoring learning approaches in improving maternal and newborn health and trainees’ satisfaction. Even in developed countries where these approaches have been tested, the studies are limited by small sample sizes. Therefore it is important that future research on health worker capacity building in Nigeria and other LMICs should include the testing of techniques to enhance knowledge, skills and satisfaction among healthcare workers using appropriately designed and statistically powered studies.

Factors known to affect skills and knowledge acquisition including motivation and learning environment [4], team leadership and communication [5], and use of simulators to enhance skills retention for low-frequency procedures [6] and others have been explored by various researchers. It has been shown that a strong health workforce leadership is an important factor to ensure motivation and create an enabling learning environment [7–9].

Apart from high cost of training generally [10], traditional off-site training can lead to service disruptions due to absenteeism to attend trainings and loss of personal income [11]. Apparently therefore, different training strategies will be associated with different costs and there is need to combine cost effectiveness, learning outcomes, and alignment with national strategy in order to inform better policy decisions [12, 13].

Maternal and Child Survival Program (MCSP), a United States Agency for International Development (USAID) multi-country cooperative agreement serves as conduit for bringing innovations into healthcare practice in Ebonyi and Kogi States, in South-East and North-Central Nigeria respectively with special emphasis on the *‘Day of Birth Care’*. The core package includes evidence-based interventions such as use of the partograph, administration of uterotonic, essential newborn care, newborn resuscitation, and the use of magnesium sulphate for severe pre-eclampsia and eclampsia. In addition to supporting clinical innovations, MCSP has an implementation research agenda for process innovations to test the effectiveness of different approaches to improve maternal and newborn health care delivery services. For example, through control and intervention demonstration learning groups, MCSP endeavors to build evidence to support the shift from group based training outside of the health facility to LDHF approach.

The authors hypothesized that simulation-based LDHF/m-Mentoring will result in better satisfaction, knowledge and skill outcomes as well as will be more cost effective compared to a group-based approach among birth attendants in Kogi and Ebonyi states.

## Methods/Design

### Study aim

The aim of this study will be to compare the effectiveness and cost of onsite LDHF plus m-Mentoring training approach versus the traditional offsite group-based training approach in improving knowledge and skill in maternal and newborn *day of birth* care and to determine trainees’ satisfaction with the approaches in Ebonyi and Kogi states of Nigeria.

The specific objectives will be to:Compare knowledge and skills learning outcomes between the two groups of birth attendants trained through the simulation-based LDHF/m-Mentoring versus group-based training approaches in Kogi and Ebonyi states over 12-months.Assess the trainees’ levels of satisfaction with a simulation-based LDHF/m-Mentoring and group-based training in the selected facilities in Kogi and Ebonyi state over 12-months.Determine the cost and cost-effectiveness of LDHF/m-Mentoring and group-based training approaches in improving skills of birth attendants in the selected facilities in Kogi and Ebonyi state over 12-months.

### Study design

The study will be a prospective cluster randomized control trial. It will include healthcare providers in 60 health facilities in Kogi and Ebonyi State randomly assigned to either LDHF (intervention) or TRAD (control) arms. For both study arms, skills and knowledge assessments will be done by independent assessors who will be blinded to the training approaches used. This will be at three time points post-training (immediate post training day, at 3 months 12 months) using MCQs (see Additional file 1) and OSCEs. Cost and trainees’ satisfaction level with training approach is determined using satisfaction (quantitative) survey. Qualitative data will also be collected through focus group discussions (FGD) and in-depth interviews (IDIs) at 12 months for the LDHF arm.

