### Training approach 1 and data collection: Simulation-based LDHF/m-mentoring training of participants - group 1 or intervention group

The training for the LDHF arm will be for the entire team of service providers available at the health facility, but only those who will meet the study inclusion criteria will be assessed. After oral consent is obtained, the participants will take pre-training assessments consisting of MCQs and OSCEs through use of manikins, to assess their baseline knowledge and skills. The MCQ contains a set of multiple choice questions to test trainees’ knowledge. OSCE involves the use of validated checklists to evaluate trainees’ demonstration of clinical skills to ensure that each step is correctly and completely carried out. The assessments will test their knowledge and skills on conduct of normal delivery, active management of the third stage of labor (AMTSL), neonatal resuscitation, case management of pre-eclampsia and eclampsia (PEE) and management of PPH (e.g. manual removal of placenta, internal bimanual uterine compression and compression of the abdominal aorta). The training will be divided into two “low-dose” training courses of 4 days each, with additional time for assessment as needed and will be conducted at the health facilities using the adapted basic emergency obstetrics and newborn care (BEmONC) package repeated after 1 month. The training techniques will be modified to shift the emphasis to practice. The time spent on lectures will be reduced and time spent on hands-on practice will be increased. The Peer Practice Coordinators (PPCs) will receive technical update in LDHF including the use of session plans, case scenario and MamaNatalie/NeoNatalie models to conduct simulation practices. At the end of the four-day training, the participants will undergo an immediate post-training assessment which includes MCQs and OSCEs. The questions answered correctly and procedure done competently is scored over a total of 100%. A test score of ≥80% is accepted as level of competence. The pre-training and immediate post-training assessments results will be compared. During the one-month intervals between training courses, health care providers will have the opportunity to practice what they learned and reinforce their competencies through high-frequency simulation-based practices of 2–3 times weekly. The PPCs will complete the practice log. In addition to the simulation exercises, all the trained providers in the LDHF arm will participate in mobile Mentoring (mMentoring), which consists of receiving weekly reminder messages and quiz questions on the topics reviewed via SMS messaging. Also the PPCs will receive structured, monthly half-hour mentoring calls from a trainer/master mentor that provide remote support, answering questions, providing guidance and reinforcing key messages. Skills and knowledge assessments will be done at three time points post-training (immediate post training day, at 3 months 12 months). Trainees’ satisfaction with the simulation-based LDHF/m-Mentoring training approach will also be determined using satisfaction (quantitative) survey.

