
Qualitative data will be collected through six (6) focus group discussions (FGD) comprising 8–10 similar participants per group purposively selected from among the trainees at 12 months based on their availability and experience. The FGD focuses on the experiences and satisfaction of trainees with LDHF training approach, and high-frequency practice sessions with simulators, mobile mentoring sms and quizzes, opinions about changes in clinical practice and outcomes and overall impressions of the LDHF approach and what could be improved. The FGD will last 60–90 min. In-depth interviews (IDIs) will also be conducted with PPCs and trainers at 12 months post-training by study staff. The IDIs for PPCs will aim at hearing their insights and experience managing simulator practice sessions for their facility, interacting and working with the trainers/master mentors, m-Mentoring, changes in clinical practice and outcomes, success and challenges and overall impression about LDHF approach. For the trainers, their thoughts and experience with the LDHF training approach, successes and challenges with mobile mentoring and supporting peer practice coordinators, opinions on the effectiveness of m-Mentoring, confidence in their role as trainers, successes and challenges in collecting data will be sought. Each IDI will last about 45 min and is audio recorded.

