### Training approach 2 and data collection: Traditional group training of participants – Group 2 or control group

The traditional training approach will consist of 8 days of lectures with practice sessions on simulators, off-site the participants’ workplace, usually in a hotel. Oral consent will be obtained, the participants will take pre-training assessments consisting of MCQs and OSCEs through use of manikins, to assess their baseline knowledge and skills respectively. The assessments will test their knowledge and skills on conduct of normal delivery, AMTSL, neonatal resuscitation, case management of PEE and management of PPH (e.g. manual removal of placenta, internal bimanual uterine compression and compression of the abdominal aorta). This group then receives lectures and practice sessions on conduct of normal delivery, AMTSL, neonatal resuscitation, case management of PEE and management of PPH. The Nigerian BEMONC package and clinical observation checklists are used during the training sessions. The group-based training approach will include training sessions consisting of 8 days of lectures and fewer practice sessions using manikins (MamaNatalie/NeoNatalie) offsite and not at the trainees’ place of work. Table 1 outlines the basic similarities and difference between the two groups. At the end of the eight-day training, the participants will undergo an immediate post-training assessment which includes MCQs and OSCEs. As described among arm 1, the questions answered correctly and procedure done competently will be scored out of a total of 100%, assessments results will be compared and trainees satisfaction survey will be conducted.

**Table 1 Tab1:** Comparison of the Simulation-based LDHF and Group-based study arms

Parameters of the interventions received	Simulation-based LDHF Arm	Group-based Arm
Training covers BEMONC	Yes	Yes
Training is onsite	Yes	No
More frequent practise sessions using manikins during training	Yes	No
Post-training Practise Sessions with manikin in facility	Yes	No
Presence of PPCs	Yes	No
Use of mobile phone for post-training support	Yes	No
All courses divided into two phases which are 1 month apart	Yes	No

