#### Inferential analysis

Generalized linear model with robust facility-level variance will be used to test the differences between arms in MCQ scores, OSCE scores and satisfaction outcomes at 3 months using a group indicator as the main predictor in the model. Additionally, we will adjust for provider- and facility-level characteristics that show imbalance between arms at baseline and can be strongly correlated with the outcome scores. A *p*-value < 0.05 will be considered statistically significant. The number of short messages sent is assessed for trend of the reply and correct answers. The frequency and trend of mentorship call will also be assessed. The model described for the primary outcome is used to look at the outcomes at other time points. In addition, we will develop a longitudinal model that assess the change in scores (or competency level) over time post-training. This model is appropriate, since it accounts for correlation within a provider over time as well as within-facility correlation of scores. Generalized linear population-average model estimated using generalized estimating equations (GEE) with working exchangeable correlation structure is used. The amount of missing data is assessed for each variable and overall for the sample. If more than 5% of data are missing, multiple imputation procedure is used assuming missing at random. Composite scores is computed for the satisfaction survey. A Decision Tree will be used to compare incremental costs and incremental effects by provider across the two study arms. One-way, multi-way and probabilistic sensitivity analyses are conducted to assess uncertainty.

Qualitative data analysis: Notes and transcripts will be entered into Atlas-ti version 8 software. Content analysis of the discussions will be undertaken to generate themes of interest along which the analysis will be done. Analysis will be by themes across location and classifications of the groups.

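### The claim of blinded assessors does not hold for the OSCE on the immediate post-training day, because that assessment closes a course whose setting identifies the arm

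*Protocol article*

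**What the plan says.** The Study design section of the protocol article makes one statement for both arms: "skills and knowledge assessments will be done by independent assessors who will be blinded to the training approaches used". The sentence that follows fixes when: "This will be at three time points post-training (immediate post training day, at 3 months 12 months". The blinding claim therefore covers the immediate assessment as well as the two later ones.

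The two training sections describe where and when the first assessment falls.

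- **LDHF:** the courses come "with additional time for assessment as needed and will be conducted at the health facilities". "At the end of the four-day training, the participants will undergo an immediate post-training assessment which includes MCQs and OSCEs".
- **TRAD:** the course is held "off-site the participants’ workplace, usually in a hotel". "At the end of the eight-day training, the participants will undergo an immediate post-training assessment which includes MCQs and OSCEs".

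The Sample size section likewise schedules the first post-training assessment for the close of training. Table 1 lists on-site training as a feature of the LDHF arm and not of the group-based arm.

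The primary outcome is competency at 3 months. The Inferential analysis section applies the primary model to the other time points and adds a "longitudinal model that assess the change in scores (or competency level) over time post-training".

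**The concern.** The OSCE is a checklist that an observer scores while a trainee works on a manikin. Competence is then declared at 80% or more on each of the MCQ and the OSCE. A small leniency or severity near the cut can change a provider's classification, so blinding of the scorer matters for this instrument. It matters much less for the MCQ.

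Venue and course format are what separate the arms. If the scorer stands in the training venue on the last day of the course, the arm is visible. A report that described the immediate between-arm OSCE comparison as blinded would then claim a protection that the design does not give. The immediate scores would also shape the estimated change over time in the longitudinal model, even if scoring at 3 and 12 months were fully blinded.

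**Working it through.** **1. The statements side by side**

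| Item | LDHF | TRAD | Section |
|---|---|---|---|
| Assessors blinded | claimed | claimed | Study design |
| Immediate day included in the claim | yes | yes | Study design |
| Course length before the first assessment | 4 days | 8 days | Training approach 1 and 2 |
| Course venue | own facility | off-site, usually a hotel | Training approach 1 and 2 |
| Masking device described | none | none | whole article |

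For LDHF, the text attaches assessment time to the on-site course. For TRAD, the OSCE venue is not stated outright. It is inferred from the assessment falling at the end of the eight-day course, on the immediate post-training day. The inference does not need a hotel, because any off-site group venue differs from the trainee's own facility. An assessor physically present would therefore learn the arm in both groups.

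**2. The plan's own figure**

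Inputs from the Sample size section: 50% against 70% competent, alpha 0.05 (taken as two-sided), 80% power, within-facility correlation 0.05, four providers per facility, 20% drop-out.

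- Design effect: 1 + (4 − 1) × 0.05 = 1.15.
- With continuity correction: 103 × 1.15 = 118.5, so 119 per arm and 238 in total, against 240 stated.
- Without continuity correction: 93 × 1.15 = 107 per arm, 214 in total; 240 then gives about 84% power.
- Drop-out: 240 / (1 − 0.2) = 300, as stated.

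The sample size reproduces, and this point does not affect it.

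**3. What a small leniency could do (illustration only)**

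Assumptions not in the documents: bivariate normal scores, OSCE standard deviation (SD) 8 to 15 points, equal pass rates on the two tests, correlation between tests 0 to 0.7, and leniency d of 2 or 3 points towards one arm.

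The plan's 50% is the rate of passing both tests. Let a be the margin, in SD units, by which the mean score exceeds the cut. It solves P(Z1 ≤ a, Z2 ≤ a) = 0.5. The shift in the competent proportion is then P(Z1 ≤ a + d/SD, Z2 ≤ a) − 0.5.

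Worked case with correlation 0: each pass rate is √0.5 = 0.707, so a = 0.545. With d = 2 and SD = 8, the joint rate becomes 0.707 × Φ(0.545 + 0.25) = 0.707 × 0.787 = 0.556, a shift of 5.6 points.

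| Leniency | Smallest shift (SD 15, correlation 0.7) | Largest shift (SD 8, correlation 0) |
|---|---|---|
| 2 points | 2.6 | 5.6 |
| 3 points | 3.8 | 8.1 |

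All are in percentage points, against a planned effect of 20.

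**4. Effect on a between-arm test at the affected time point (illustration only)**

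Take 120 per arm, so the effective number is 120 / 1.15 = 104.3, with no true difference at 50%. A pure scoring shift of 2 points in the competent proportion takes the two-sided type I error from 5% to about 6%. A shift of 5 points takes it to about 11%.

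**The case against.** The strongest defence has four parts.

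- **The time point is not a main one.** The immediate OSCE is neither the primary outcome (3 months) nor the listed competency secondary (12 months). This stands and limits the weight of the point. The immediate scores still enter the other-time-point comparisons and the longitudinal model.
- **The TRAD OSCE venue is inferred, and remote or video scoring is not ruled out.** This also stands as a caveat. As written, however, the article claims blinding in settings that reveal the arm and names no device to achieve it.
- **Assessor rosters belong to the full protocol.** This is correct. A reader might infer that assessors unblinded on the training day go on to score the 3-month primary OSCE. The documents do not support that. They describe independent blinded assessors at 3 months and do not say whether the same people attend both occasions. Carry-over is a possibility that the article leaves open, no more.
- **Trainers are not shown to score anything.** Trainers are to be interviewed at 12 months, and among the topics "successes and challenges in collecting data will be sought". A reader might infer that trainers take part in OSCE scoring. That over-reads an interview topic: it does not mention OSCEs, and the Study design section gives assessment to independent assessors.

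A reader might also compute a larger effect by treating 50% as the OSCE pass rate. Φ(d/SD) − 0.5 then gives about 5 to 10 points for a 2-point leniency and 8 to 15 for 3 points. This is not right here: 50% is the rate of passing both tests, and OSCE leniency cannot rescue an MCQ failure. The OSCE and MCQ scores are also analysed as such, so the 80% cut is not the only route to a conclusion.

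**Conclusion.** The point holds for the immediate post-training OSCE. The article states a blinding that its own description of venue and timing does not allow there, on the reasonable inference that the TRAD OSCE takes place where the course ends and that no undescribed masking is in use. The MCQ is little affected and the sample size is untouched.

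The possible bias cannot be estimated from the documents. Under the assumptions in the working, leniency of 2 to 3 OSCE points would move the competent proportion by roughly 3 to 8 percentage points. That is smaller than the planned 20 but large enough to disturb a between-arm comparison at that time point.

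No fault is shown in the 3-month primary assessment. It carries only the unaddressed risk that a training-day assessor returns to the same facility.

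**What to change.** 1. Limit the blinding statement to the 3- and 12-month assessments, and report the immediate between-arm OSCE comparison as unblinded. If the full protocol contains a masking method for that day, state it instead. Cost: a change of wording.
2. Fit the longitudinal between-arm contrast with and without the immediate OSCE and report both. Cost: one further model run.
3. Where existing rosters allow, assign the existing assessors so that nobody scores, at 3 or 12 months, a facility whose trainees they assessed on a training day. If this is already arranged, one sentence saying so is enough. Cost: some scheduling and travel. The documents give no number of assessors and no rota, so this cost cannot be put in figures.

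Recording each assessor's guess of the arm at 3 and 12 months would be a useful check but is optional. None of these changes needs more participants.
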